### **Procedures for Discontinuation of Participation**

If any discontinuation criteria are met, the principal investigator stops the study and record the discontinuation date and reason in the medical records. If the participant voluntarily withdraws from the study, no further data is collected from that point forward.

# **Observation and Examination Items and Schedule**

## **Visit 1. Consent Acquisition, Eligibility Confirmation, and Provisional Registration**

From 30 days before surgery to the day of surgery, the following data are collected from routine medical records to confirm eligibility and obtain consent.

| 1) Basic Subject Information | |
| --- | --- |
| Subject information | Date of obtaining consent, date of birth, age, gender |
| 2) Target Disease Information | |
| Disease information | Diagnosis, planned procedure, medical history, comorbidities |
| 3) Clinical and Laboratory Data**^*^** | |
| Physical findings | Height, weight, body surface area |
| Laboratory tests | Hemoglobin, platelet count, PT-INR, APTT, ABO and RhD blood type, presence of irregular antibodies |
| 4) Oral Medication Information | |
| Oral medecations | Use and withdrawal periods for steroids, immunosuppressants, antiplatelet and anticoagulant drugs |

- Laboratory results within 90 days prior to consent are used, with priority given to those closest to the consent date.

## **Visit 2. Final Registration and Randomization (Baseline)**

The following data are collected up to the time of CPB weaning on the day of surgery.

| 1) Clinical and Laboratory Data**^*2^** | |
| --- | --- |
| Physical findings | Height, weight, body surface area |
| Laboratory tests | White blood cell count, hemoglobin, platelet count, total protein, albumin, total bilirubin, direct bilirubin, AST, ALT, creatinine, LDH, CK, CK-MB, sodium, potassium, chloride, calcium, CRP, PT-INR, APTT, fibrinogen, D-dimer, FDP, ATIII activity |
| 2) Oral Medication Information | |
| Oral medications | Discontinuation period of antiplatelet agents and anticoagulants |
| 3) Surgical Information | |
| Treatment Information | Use of allogeneic RBC transfusion during CPB |

*2 Information are collected prior to the induction of general anesthesia. If results obtained during routine clinical care are available within 14 days before the day of surgery, those results are used.

## **Visit 3. During Study Treatment**

The following information is collected after weaning from CPB on the day of surgery (allowable range: +3 days). Data isobtained from the anesthesia records (ORSYS) and electronic medical records (MegaOak).

| 1) Study Treatment Information | |
| --- | --- |
| Treatment Information | - Volume of salvaged RBC and transfused allogeneic RBC (a) during from the start of general anesthesia to weaning from CPB, and (b) from weaning from CPB to leaving the operating room - Intraoperative blood loss - Heparin concentration in salvaged RBC (salvaged RBC group only)^*3^ |
| 2) Clinical and Laboratory Data |  |
| Vital signs | Blood pressure, heart rate, peripheral oxygen saturation (SpO₂), central venous pressure, pulmonary artery pressure, cardiac output (at the end of surgery) |
| Physical findings | Gross hematuria upon ICU admission |
| Blood gas analysis | Hemoglobin (at the following time points: after induction of general anesthesia, before initiation of CPB, during CPB, after CPB following protamine administration, and additionally as needed) |
| Laboratory tests | Hemoglobin, platelet count, PT-INR, APTT, fibrinogen, and blood viscoelastic testing (at the following time points: before and after weaning from CPB following protamine administration, at ICU admission, and additionally as needed)  Total protein, albumin, total bilirubin, direct bilirubin, AST ALT, creatinine, LDH, CK, CK-MB, sodium, potassium, chloride, calcium, and CRP (laboratory data collected at the time of ICU and subsequently as required). |
| 2) Concomitant Treatment Information | |
| Concomitant Therapy | - Volume of transfused FFP, platelet concentrates, and cryoprecipitate during (a) from the start of general anesthesia to weaning from CPB, and (b) from weaning from CPB to leaving the operating room - Total intraoperative doses of colloid solutions, tranexamic acid, heparin (excluding that used in the salvage system), and protamine |
| 3) Surgical Information | |
| Surgical Information | Definitive diagnosis, definitive surgical procedure, operative time, CPB time, aortic cross-clamp time, lowest temperature during CPB |
| 4) Adverse Events | |
| AEs | Date of onset, event name, known/unknown, seriousness, severity, causal relationship, treatment, outcome, date of outcome confirmation, other details |

*3 Measured for research purposes

## **Visit 4. End of Study**

Observations and examinations are performed 30 days after the initiation of study treatment (acceptable range: ±5 days). Data is collected from the critical care information system (AXIS) and electronic medical record system (MegaOak).

| 1) Study Treatment Information | |
| --- | --- |
| Treatment Information | - Postoperative chest tube blood loss within 12 hours after ICU admission - Total chest tube blood loss until removal - Transfusion volume within 24 hours after ICU admission (RBC, FFP, cryoprecipitate, platelet concentrates) - Duration of mechanical ventilation - Length of ICU stay - Postoperative hospital stay - Date of discharge |
| Discontinuation/interruption of treatment | Presence or absence; if applicable, record the date, reason, and subsequent management |
| 2) Clinical and Laboratory Data | |
| Laboratory tests  (obtained on the day after surgery) | White blood cell count, hemoglobin, platelet count, total protein, albumin, total bilirubin, direct bilirubin, AST, ALT, creatinine, LDH, CK, CK-MB, sodium, potassium, chloride, calcium, CRP, PT-INR, APTT, fibrinogen |
| 3) Adverse Event Reports | |
| AEs | Date of onset, event name, known or unknown, seriousness, severity, causal relationship, treatment, outcome, date of outcome confirmation, readmission status (presence/absence), date of readmission, date of discharge, and other relevant details |
| 4) Outcome Information | |
| Survival status | Outcome: alive, deceased, or lost to follow-up  Date of last confirmed survival or date of death; in case of death: cause of death If lost to follow-up: reason for discontinuation of follow-up |
| Stuidu withdrawal | Presence or absence; if applicable, record the date and reason for withdrawal |

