**Observation Period**: **30days**

The primary outcome will be the measurement of the total drainage volume within 12 hours of ICU admission. As a secondary outcome, patients will be followed for 30 days after the administration of the investigational treatment.

Abbreviations

| AE | Adverse event |
| --- | --- |
| ACT | Activated clotting time |
| ALT | Alanine aminotransferase |
| APTT | Activated partial thromboplastin time |
| AST | Aspartate aminotransferase |
| ATIII | Anti thrombin III |
| BNP | Brain natriuretic peptide |
| CABG | Coronary artery bypass grafting |
| CDC | Centers for disease control and prevention |
| CK | Creatine kinase |
| CPB | Cardiopulmonary bypas |
| CRF | Case report forms |
| CRP | C-reactive protein |
| FAS | Full analysis set |
| FBS | Fast blood sugar |
| FDP | Fibrin/fibrinogen degradation products |
| FFP | Fresh frozen plasma |
| ICU | Intensive care unit |
| ITT | Intent-to-treat population |
| LDH | Lactate dehydrogenase |
| PPS | Per protocol set |
| PT-INR | Prothrombin time-international normalized ratio |
| RBC | Red blood cell |
| SAE | Serious adverse event |
| SSI | Surgical site infection |

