## **When the study is stopped early (date of decision to discontinue+3)**

The following observations and tests are performed within three days of study discontinuation.

| 1) Study Treatment Information | |
| --- | --- |
| Discontinuation/interruption of treatment | Presence or absence; if applicable, record the date of discontinuation/interruption, reason, and subsequent management. |
| 2) Clinical and Laboratory Data ^*4^ | |
| Laboratory tests | White blood cell count, hemoglobin, platelet count, total protein, albumin, total bilirubin, direct bilirubin, AST, ALT, creatinine, LDH, CK, CK-MB, sodium, potassium, chloride, calcium, CRP, PT-INR, APTT, fibrinogen |
| 3) Adverse Event Information | |
| AEs | Date of onset, event name, known or unknown, seriousness, severity, causal relationship, treatment, outcome, date of outcome confirmation, readmission status (presence or absence), date of readmission, date of discharge, and other relevant details |
| 4) Outcome Information | |
| Survival status | Outcome: alive, deceased, or lost to follow-up  Date of last confirmed survival or date of death; in case of death: cause of death  If lost to follow-up: reason for loss to follow-up |
| Study withdrawal | If applicable, record the date of withdrawal and the reason |

*4 If test results from other visits or routine clinical care are available within one day prior to the date of study discontinuation, those results are used be used.**Observation and Inspection Schedule**

| Survey Period  Survey Items | Test Period | | | | Early discontinuation |
| --- | --- | --- | --- | --- | --- |
|  | Visit 1 | Visit 2 | Visit 3 | Visit 4 |  |
|  | **Consent, eligibility check, provisional registration** | **Final registration, allocation (prior to study treatment initiation)** | **During study treatment** | **End of Exam** |  |
| Stipulated days | -30 days~ | 0 days | 0 days | 30 days | ― |
| Tolerance | ― | ― | +3 days | ± 5 | +3 days |
| **Informmed consent** | ◎ |  |  |  |  |
| **Basic subject information** | ○ |  |  |  |  |
| **Target disease information** | ○ |  |  |  |  |
| **Study treatment information** |  |  | ○ | ○ | ○ |
| **Oral medication information** | ○ | ○ |  |  |  |
| **Physical findings** | ○^※1^ | ○^※2^ | ○ |  |  |
| **Vital signs** |  |  | ○ |  |  |
| **Laboratory tests (complete blood count, biochemistry, blood type-related, coagulation, viscoelastic testing)** | ○^※1^ | ○^※2^ | ○ | ○^※3^ | ○^※4^ |
| **Blood gas analysis** |  |  | ○ |  |  |

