## **Reporting of AEs**

### **Reporting Period for AEs**

AEs must be reported from the initiation of study product administration until 30 days thereafter or until the final study visit specified in the protocol, whichever is later. Any SAE for which a causal relationship with the study product cannot be ruled out must be reported **regardless of the reporting period**, as long as it occurs before the end of the study period.

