# **Study Period**

Planned Study Period: From the date of ethical approval to March 31, 2030

Enrollment Period: From the date of ethical approval to September 30, 2026

Observation Period: From the date of ethical approval to November 4, 2026

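### The End of Study visit may be completed on day 25, before the promised 30 days of follow-up have passed, and no later check of survival or adverse events is scheduled

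*Protocol*

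**What the plan says.** All of these places are in the Protocol.

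- **Study Overview, Observation Period:** "patients will be followed for 30 days after the administration of the investigational treatment".
- **Section 8.4, Visit 4 (End of Study):** "Observations and examinations are performed 30 days after the initiation of study treatment (acceptable range: ±5 days"). The schedule table repeats the window in its tolerance row: "Tolerance | ― | ― | +3 days | ± 5 | +3 days". The ± 5 entry belongs to Visit 4.
- **Section 8.4, source and content:** "Data is collected from the critical care information system (AXIS) and electronic medical record system (MegaOak"). Survival is recorded with dates: "Date of last confirmed survival or date of death; in case of death: cause of death". Visit 4 also collects AEs and readmission.
- **Section 9.4.1, AE reporting period:** from first administration "until 30 days thereafter or until the final study visit specified in the protocol, whichever is later". Serious adverse events (SAEs) for which a causal link cannot be ruled out "must be reported regardless of the reporting period, as long as it occurs before the end of the study period".
- **Sections 4.3 and 4.4:** infection (safety outcome 1) and mortality (an experimental outcome) have no time point. Acute kidney injury has 7 days, and haematuria is assessed at ICU admission.
- **Section 10, Study Period:** enrollment closes on 30 September 2026. "Observation Period: From the date of ethical approval to November 4, 2026".

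**The concern.** The length of follow-up and the timing of the visit that closes it do not agree. A site can follow section 8.4 to the letter, complete Visit 4 on day 25, and stop five days short of the period that the Study Overview promises. No visit, telephone contact or record check comes afterwards.

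What is at stake is ascertainment of late events. A patient last confirmed alive on day 25 has unknown day-30 status, and an analysis rule cannot recover information that was never collected. Because mortality and infection carry no time point in the outcome lists, the protocol itself sets no common horizon for them.

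**Working it through.** **Inputs.** Visit 4 at day 30 with a window of ±5 days (section 8.4 and the schedule table). Follow-up of 30 days (Study Overview). AE reporting to day 30 or the final visit, whichever is later (section 9.4.1). Enrollment to 30 September 2026 and observation to 4 November 2026 (section 10).

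**1. The plan's own end date.** Assume that the last final registration, and so the last study treatment, is on 30 September 2026.
- Earliest Visit 4: 30 September + 25 days = 25 October 2026.
- Nominal Visit 4: 30 September + 30 days = 30 October 2026.
- Latest Visit 4: 30 September + 35 days = 4 November 2026.

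The last date equals the stated end of observation exactly, so the calendar already allows for a visit on day 35.

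**2. The shortfall.** Earliest visit = 30 − 5 = day 25. Days of promised follow-up after that visit = 30 − 25 = 5, or 5/30 = 17% of the period. This is a worst-case share of days for one patient, not a share of events. The protocol gives no event rate for days 26 to 30.

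**3. The horizon, by type of information.**

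| Information | Shortest | Longest | Spread |
|---|---|---|---|
| Survival status confirmed at Visit 4 | day 25 | day 35 | 10 days |
| AE reporting duty, including infections reported as AEs | day 30 | day 35 | 5 days |

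The second row starts at day 30 because of the whichever-is-later clause. The 25-to-35-day spread therefore applies to survival status, not to the AE reporting duty.

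**4. What dated records can repair.** If Visit 4 falls on day 30 or later, onset and death dates allow every event to be cut at day 30. If it falls on days 25 to 29, a day-30 cut needs a further look at the records, and none is scheduled.

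**5. Effect of a 0 to +5 day window.** Earliest visit = day 30, so the shortfall drops from 5 days to 0. The spread in visit day drops from 10 days to 5. The latest visit stays at day 35, so 4 November 2026 still holds.

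**The case against.** The strongest reply is that event capture does not depend on the visit. Section 9.4.1 keeps AE reporting open to day 30 even when Visit 4 is early. Section 9.2 requires prompt recording of all AEs in the study period. Death is an SAE under section 9.3.1, with its own reporting route in section 9.4.2. This stands: events on days 26 to 30 are inside the plan, and a reader who infers that they fall outside it goes too far. It does not close the gap in ascertainment. The SAE procedure starts when staff learn of an event, and for a discharged patient whose records were reviewed on day 25 nothing prompts a second look.

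The adverse-event row of the schedule table is blank in the text at hand, and the legend has an arrow for items assessed throughout. The arrow was probably lost when the PDF was read, so nothing here rests on that blank row. Even with the arrow, no check is scheduled after an early Visit 4.

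A reader might also infer that missed late events favour the salvaged group in a non-inferiority trial. The document does not support this. The 200 mL margin applies to 12-hour drainage only, the window is the same in both groups, and section 7.4 blinds outcome assessors and postoperative physicians. No differential loss is shown.

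Finally, an analysis cut-off can be left to the statistical analysis plan, which is not at hand. That is fair for late visits, but a cut-off cannot supply a survival status that was not collected.

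**Conclusion.** The point holds in a limited form. The protocol permits the final visit up to five days before its own 30-day follow-up and minimum AE reporting period end, with no later check scheduled, so confirmed survival can range from 25 to 35 days between patients.

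It touches mortality and the completeness of late infection and AE records. It does not touch the primary or secondary outcomes (all within 48 hours), acute kidney injury, haematuria, the margin, power or sample size.

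The conclusion assumes that some Visit 4 reviews are actually completed before day 30 and that no unscheduled check follows. How many patients or events this would affect cannot be estimated from the document. It is a minor improvement, worth making because it costs so little.

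**What to change.** Change the Visit 4 window from ±5 days to 0 to +5 days (day 30 to 35) in section 8.4 and in the tolerance row of the schedule table, so that survival and AE records are reviewed no earlier than day 30. State that mortality and infection (safety outcome 1) are counted to day 30 for every patient, using the recorded dates. The cut-off is still needed, because visits will fall anywhere from day 30 to day 35.

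The cost is a wording change to the window in two places and one sentence on the cut-off. Visit 4 draws on electronic records and its laboratory values come from the day after surgery, so no attendance has to be moved, and the end of observation stays at 4 November 2026. The downside is a narrower window for completing the form: 5 days in place of 10. A record review on or after day 30 does not by itself prove that a discharged patient is alive, but without one day-30 status cannot be established.

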## **When the study is stopped early (date of decision to discontinue+3)**

The following observations and tests are performed within three days of study discontinuation.

| 1) Study Treatment Information | |
| --- | --- |
| Discontinuation/interruption of treatment | Presence or absence; if applicable, record the date of discontinuation/interruption, reason, and subsequent management. |
| 2) Clinical and Laboratory Data ^*4^ | |
| Laboratory tests | White blood cell count, hemoglobin, platelet count, total protein, albumin, total bilirubin, direct bilirubin, AST, ALT, creatinine, LDH, CK, CK-MB, sodium, potassium, chloride, calcium, CRP, PT-INR, APTT, fibrinogen |
| 3) Adverse Event Information | |
| AEs | Date of onset, event name, known or unknown, seriousness, severity, causal relationship, treatment, outcome, date of outcome confirmation, readmission status (presence or absence), date of readmission, date of discharge, and other relevant details |
| 4) Outcome Information | |
| Survival status | Outcome: alive, deceased, or lost to follow-up  Date of last confirmed survival or date of death; in case of death: cause of death  If lost to follow-up: reason for loss to follow-up |
| Study withdrawal | If applicable, record the date of withdrawal and the reason |

*4 If test results from other visits or routine clinical care are available within one day prior to the date of study discontinuation, those results are used be used.**Observation and Inspection Schedule**

| Survey Period  Survey Items | Test Period | | | | Early discontinuation |
| --- | --- | --- | --- | --- | --- |
|  | Visit 1 | Visit 2 | Visit 3 | Visit 4 |  |
|  | **Consent, eligibility check, provisional registration** | **Final registration, allocation (prior to study treatment initiation)** | **During study treatment** | **End of Exam** |  |
| Stipulated days | -30 days~ | 0 days | 0 days | 30 days | ― |
| Tolerance | ― | ― | +3 days | ± 5 | +3 days |
| **Informmed consent** | ◎ |  |  |  |  |
| **Basic subject information** | ○ |  |  |  |  |
| **Target disease information** | ○ |  |  |  |  |
| **Study treatment information** |  |  | ○ | ○ | ○ |
| **Oral medication information** | ○ | ○ |  |  |  |
| **Physical findings** | ○^※1^ | ○^※2^ | ○ |  |  |
| **Vital signs** |  |  | ○ |  |  |
| **Laboratory tests (complete blood count, biochemistry, blood type-related, coagulation, viscoelastic testing)** | ○^※1^ | ○^※2^ | ○ | ○^※3^ | ○^※4^ |
| **Blood gas analysis** |  |  | ○ |  |  |
| **Heparin concentration in salvaged RBC**  **(Salvaged RBC group only)** |  |  | ● |  |  |
| **Concomitant treatment information** |  |  | ○ |  |  |
| **Surgery Information** |  | ○ | ○ |  |  |
| **Adverse events** |  |  |  |  |  |
| **Outcome information** |  |  |  | ○ | ○ |

　➡ : Assessed throughout the study period ◎: Mandatory items ○: Routine clinical examination item ●: Study-specific examination

*1 Results obtained from routine clinical care within 90 days before obtaining informed consent may be used for the study.

*2 Information must be collected before the induction of general anesthesia. If results from routine clinical care are available within 14 days before the day of surgery, they are used.

*3 Data obtained on the day after surgery is used.

*4 To be performed whenever possible. If results from other visits or routine clinical care are available within one day prior to the date of study discontinuation, they are used.

## **Definition of observation and inspection items**

### **Definition of the disease**

|  | definition |
| --- | --- |
| Myocardial infarction | A confirmed diagnosis of the above condition made by a cardiologist |
| sStroke | A confirmed diagnosis of the above condition made by a neurosurgeon or neurologist. |
| Heart failure | A history of hospitalization for the above condition, or classified as New York Heart Association Class II or higher, or with a left ventricular ejection fraction of less than 50% as determined by echocardiography. |
| Known coagulation and fibrinolytic disorders | Confirmed diagnoses of any of the following: idiopathic thrombocytopenic purpura, thrombotic thrombocytopenic purpura, aplastic anemia, antiphospholipid antibody syndrome, protein C deficiency, or other congenital or acquired coagulation or fibrinolytic disorders. |

# **Evaluation and Reporting of AEs**

## **Definition of AEs**

An AE refers to any untoward medical occurrence in a subject who has received the study treatment, regardless of whether a causal relationship with the study treatment can be established. A side effect is defined as an AE for which a causal relationship with the study product cannot be reasonably excluded.

## **Response to the Occurrence of AEs**

If an AE occurs, appropriate and optimal care must be provided promptly. For all AEs that occur during the study period, the following information must be promptly recorded in the medical record or related documents:
(1) name of the adverse event, (2) date of onset, (3) known or unknown event, (4) seriousness, (5) severity, (6) causal relationship with the study product, and (7) measures taken in response. Each AE must be assessed to determine whether it meets the criteria for an SAE. If judged to be an SAE, it is reported following the procedures described in Section 9.4.2.
In principle, all AEs judged to be causally related to the study product must be followed until resolution or stabilization, and the outcome and date of resolution must be documented.

